#### Sampling strategy

In this study stratified random sampling technique will be used for selection of participants where stratification will be done based on environmental factors that are likely to affect exposure. Since both distance from fixed contamination source as well as local environment features such as meteorology, topography, etc. are the major factors affecting the dispersion of both ambient air as well as water pollutants [26], a map of the study area was created to assist in selection of exposure monitoring locations and in participant sampling (see Fig 3). Briefly, taking Birlagram industrial region as the centre, villages located within consecutive circles of radius 2 kilometres (km), 5km and 10km were demarcated on the map using ArcInfo (version 10). This strategy was used as it is expected that gaseous pollutants’ dispersion occurs homogenously in all directions independent of anthropogenic roadways and that with increase in distance the pollutant concentration will become diluted enough to prevent adverse health effects [27]. Based on seasonal wind pattern data retrieved from local authorities, the north-eastern quadrant of the circular study area was seen to be the downwind area for most of the year. The downstream direction of River Chambal falls in the north-western quadrant of the circular study area. Therefore the majority of the pollutants are expected to disperse in the northern direction increasing the potential risk faced by the residents and so, we decided to over-represent the northern hemisphere.

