### Participant selection and sampling strategy

#### Sample size calculation

As the health effects of residing near textile manufacturing industries in Birlagram, India are not previously documented, we calculated the sample size using the statistics reported by a previous study conducted in Taiwan where authors [24] found that 26.3% of the population exposed to emissions from a viscose rayon manufacturing industry had electrocardiogram (ECG) abnormalities. Since one of our outcomes is the identification of the proportion of exposed population in Birlagram, India with ECG abnormalities, we calculated sample size as follows:

$$\text{Sample}\;\text{size}\;\left(\text{n}\right)=\frac{{\text{z}}^{2}\text{pq}*\left(1+\text{R}\right)*\text{Deff}}{{\text{d}}^{2}}$$

Where, p = Expected population proportion = 0.26; q = 1-p = 0.74; z = z value for 5% level of significance is 1.96; R = Non-response rate (assumed to be 30% as pooled non-response rate reported by a systematic review of participation response in Indian industrial surveys [25]); Deff = Design effect(1.25 for systematic sampling); and d = Margin of error 2% (assumed to be 0.02). The calculated sample size was 3003.

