**Fig 3 pone.0264154.g003:**
[figure not shown]
Map of the study area created by research team to assist in selection of exposure monitoring locations and in participant sampling. [Note: The inset in the map shows the Ujjain district of the central Indian province of MP. Within the Khachrod Tehsil of the Ujjain district, lies the study area of the current project. Considering the Birlagram industrial region as the centre, three concentric circular regions were demarcated based on distance (2, 5 and 10 km from the centre)].

Finally, 2000 participants will be selected from the villages in the northern hemisphere while 1003 will be taken from the villages in the southern hemisphere within the 10km radius comprising a total of 3003 participants. In each hemisphere, a fixed number of villages will be selected randomly from those situated in each of the 0-2km, 2-5km and 5-10km zones. Further in each selected village, using the list of all individuals residing in the villages that will be retrieved from the local authorities as the sampling frame, individuals meeting the eligibility criteria will be randomly invited for participation in the study. Total number of individuals sampled in each village will be proportionate to the total population of the selected village.

Participants will be selected for the study only if they fulfill all the following criteria:

Adults (≥18 years of age) of both genders (except pregnant women),Should have been residing for at least one year in the selected village,No history of neuropsychiatric conditions that might hinder completion of neurobehavioral tests,No history of other conditions that are contraindications for performing Pulmonary function test (PFT) like presence of any active disease (e.g. pulmonary Tuberculosis, active haemoptysis, orofacial pain, acute respiratory infection including COVID-19 i.e. coronavirus disease caused by SARS-Cov-2 virus) or recent history (within previous 1 month) of myocardial infarction/aneurysm/surgery, etc.

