#### Data management and analysis

All participants’ data will be coded by assigning unique identifiers. These codes will be used to identify and link various parameters of the individual participants. Data from the filled questionnaires/clinical proforma as well as the laboratory analysis values will be entered into the latest version of Microsoft Excel spreadsheets. Statistician of the team will supervise data entry and to ensure error-free data at least 10% of the entered data will be randomly verified.

Once data entry is complete, hard copies of questionnaire/proforma will be stored in a secure archive in the institute. Similarly, all entered data will be stored in password protected computer systems with access restricted to the research team alone. The data collected/generated in this study will be stored for a period of ten years. The primary investigator will be in-charge of data safety and back-up maintenance. Anonymized data set will be shared publicly during publication of study results.

All statistical analyses will be performed using IBM SPSS Statistics (version 25). For ordinal and continuous variables, the values will be given as descriptive statistics (like mean, median, standard deviation, 95% confidence interval, interquartile range); and categorical variables will be given as numbers (percentages) and proportions. Association for different health aspects with pollution level of various parameters of air/water will be made using Pearson’s chi-square test for independent categorical data. By considering the variability within and between groups; t-test and ANOVA will be used to analyze the mean differences between two and more groups respectively for various anthropological parameters, the concentration of air/water pollutants, etc. The Mann–Whitney U test and Wilcoxon signed ranks test will be used for independent and dependent for ordinal and continuous data with respect to different health aspects. Pearson and Spearman’s correlation coefficient will be used to examine the association between different variables. Multiple linear and logistic regression models will be used to estimate the relationship for different neurological assessments with a set of the independent variable. For all statistical tests, two-sided P-values <0.05 will be considered to be significant.

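### The north is deliberately over-sampled and no weighting is named, so an unweighted overall prevalence would describe the sample mix, not the exposed population

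*Protocol article*

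**What the plan says.** Three parts of the protocol article bear on this.

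- **Target (Sample size calculation).** The study is sized on the statement that "one of our outcomes is the identification of the proportion of exposed population in Birlagram, India with ECG abnormalities". The inputs are "p = Expected population proportion = 0.26", a 2-point margin of error, 30% non-response and a design effect of 1.25, giving 3003.
- **Design (Sampling strategy).** Wind and river direction lead the authors to expect more pollutant dispersion, and so more risk, to the north. Hence "we decided to over-represent the northern hemisphere": 2000 participants from northern villages and 1003 from southern ones. On the first stage: "In each hemisphere, a fixed number of villages will be selected randomly" from each of the 0-2, 2-5 and 5-10 km zones. How many is not stated. Within a selected village, the number sampled is proportional to its population.
- **Reporting (Data management and analysis).** "categorical variables will be given as numbers (percentages) and proportions". The section then lists chi-square, t-tests and ANOVA, rank tests, correlations and regression models, the last for neurological assessments. Neither this section nor any other part of the article mentions sampling weights, standardisation to stratum populations or a survey-design analysis.

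**The concern.** The stated target is a single population proportion, and the stated design gives residents unequal chances of selection. The link between the two would be a weighted estimate, and none is named. If the plan is followed as written, the overall percentage averages the strata in the proportions in which they were sampled.

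The imbalance is not neutral. The north is over-sampled because risk is expected to be higher there, so the stratum with too much influence is the one expected to have more of the outcome. The error does not shrink as the sample grows. The Discussion acknowledges an ongoing dispute between residents, manufacturers and authorities. An overall prevalence that depends on the chosen allocation would be easy to challenge in that setting.

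**Working it through.** **1. The plan's own figure.** n = z²pq(1+R)Deff/d² = 1.96² × 0.26 × 0.74 × 1.30 × 1.25 / 0.02² = 3002.7, rounded up to 3003. It reproduces. The formula has no separate term for unequal selection probabilities; its only design allowance is 1.25, labelled as being for systematic sampling.

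**2. Hemisphere bias.** Let a = 2000/3003 = 0.666 be the northern share of the sample, W the northern share of the population, and p_N and p_S the two prevalences.

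- Unweighted estimate: a·p_N + (1 − a)·p_S
- Population value: W·p_N + (1 − W)·p_S
- Difference: (a − W)(p_N − p_S)

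This takes response to be similar in both hemispheres and leaves zones aside. The document gives neither W nor the gap, so both are assumed here:

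| Northern population share W | Gap 4 points | Gap 8 points |
|---|---|---|
| 60% | 0.26 | 0.53 |
| 50% | 0.66 | 1.33 |
| 40% | 1.06 | 2.13 |

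(bias in percentage points)

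The gap at which bias equals the whole 2-point margin is 0.02/(0.666 − W): about 7.5 points at W = 40%, 12 points at 50% and 30 points at 60%.

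**3. Effect on the interval.** If the 2-point margin is achieved, the standard error is 2/1.96 = 1.02 points. A nominal 95% interval then covers the population value about 90% of the time at a bias of 0.67 points, 74% at 1.33 points and 50% at 2.0 points.

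**4. Zones.** Within a hemisphere, allocation proportional to village population gives a common within-village fraction. A resident's chance of selection is then (villages drawn / villages in the zone) × that fraction. It varies by zone unless villages are drawn in proportion to each zone's village count.

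An illustration only: by area the three zones hold 4%, 21% and 75% of the circle (4, 25 − 4 and 100 − 25, out of 100). Suppose population follows area, each zone supplies a third of the sample, and prevalences are 30%, 28% and 25%.

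- Population value: 0.04 × 30 + 0.21 × 28 + 0.75 × 25 = 25.83%
- Unweighted value: (30 + 28 + 25)/3 = 27.67%
- Difference: 1.84 points

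**5. Precision cost of weighting.** For hemisphere weights, with similar variance in both, the factor is W²/a + (1 − W)²/(1 − a).

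| W | Variance factor | Margin if 3003 is kept (2 × √factor) | N to keep 2 points |
|---|---|---|---|
| 60% | 1.02 | 2.02 | 3062 |
| 50% | 1.12 | 2.12 | 3375 |
| 40% | 1.32 | 2.30 | 3958 |

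Under the area illustration in step 4, zone weights alone would give 3 × (0.04² + 0.21² + 0.75²) = 1.82.

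**The case against.** The strongest reply is that the article never says its percentages are unweighted. A weighted prevalence is also a percentage, and weighting could sit in an analysis plan that is not shown. A reader might infer that the plan commits to raw figures; the text does not go that far. What remains is that the article itself fixes the target, the risk-driven allocation and a list of analysis methods, and nothing in that list turns the sample mix into the population figure.

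Second, over-sampling the more exposed side is legitimate, and none of the four objectives in the Introduction is a prevalence. This stands. ECG abnormality is described as one outcome among several, so calling it the study's headline result would be too strong; it matters here because it determined the sample size. Estimates within a hemisphere or zone, and associations adjusted for stratum, are much less affected.

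Third, the shares and gaps above are assumptions, and five of the six scenarios fall below the 2-point margin. This also stands. A reader might infer that the prevalence is certain to be overstated by a material amount. The documents do not support that: with equal prevalence across strata, or a northern population share of 66.6%, there is no hemisphere bias. The protocol supports only the direction, through its expectation of higher northern risk and its own description of the allocation as over-representation.

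Fourth, the zone effect rests on village numbers that are not given. A reader might infer that zones with few villages are over-represented, but if villages are drawn in proportion to each zone's count, that imbalance disappears.

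Finally, whether the exposed population means everyone within 10 km is not spelled out. That is a reason to define the target, not to leave the estimate unweighted.

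**Conclusion.** The concern holds in a limited form. Under the stated design, an unweighted overall prevalence, including the ECG proportion behind the sample size, would estimate the sample mix and not the exposed population. If prevalence is higher in the north, as the protocol expects, it would be overstated.

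The size cannot be established from the document. On assumed northern shares of 40-60% and assumed gaps of 4-8 points it is about 0.3-2.1 points, which ranges from minor to the whole margin of error. A zone effect may add to this but is conditional on unstated village numbers and zone populations. The sample-size arithmetic and the decision to over-sample are not at fault; what is missing is an estimator that matches the target under this design.

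**What to change.** - Define the population to which the overall prevalence refers.
- Record selection probabilities at both stages. Each participant's design weight is (villages in stratum / villages drawn) × (village population / people sampled there), a stratum being a hemisphere-by-zone cell. The population term should count eligible residents where the lists allow it.
- Report overall prevalences and means with these weights and design-based intervals, with stratum and village declared.
- Report prevalence separately by hemisphere and zone.
- Adjust for non-response by sex and age only if the resident lists carry those variables; the article mentions only a list of residents.

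**Cost.** The change is mainly analysis wording and record-keeping. Resident lists are to be obtained anyway, and village populations are already needed for the allocation. The price is precision: hemisphere weighting alone multiplies the variance by about 1.02, 1.12 or 1.32 at northern shares of 60%, 50% or 40%, and zone weights could add to that. The 2-point margin for the overall figure should be restated once stratum populations and village numbers are known.

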**Fig 3 pone.0264154.g003:**
[figure not shown]
Map of the study area created by research team to assist in selection of exposure monitoring locations and in participant sampling. [Note: The inset in the map shows the Ujjain district of the central Indian province of MP. Within the Khachrod Tehsil of the Ujjain district, lies the study area of the current project. Considering the Birlagram industrial region as the centre, three concentric circular regions were demarcated based on distance (2, 5 and 10 km from the centre)].

Finally, 2000 participants will be selected from the villages in the northern hemisphere while 1003 will be taken from the villages in the southern hemisphere within the 10km radius comprising a total of 3003 participants. In each hemisphere, a fixed number of villages will be selected randomly from those situated in each of the 0-2km, 2-5km and 5-10km zones. Further in each selected village, using the list of all individuals residing in the villages that will be retrieved from the local authorities as the sampling frame, individuals meeting the eligibility criteria will be randomly invited for participation in the study. Total number of individuals sampled in each village will be proportionate to the total population of the selected village.

Participants will be selected for the study only if they fulfill all the following criteria:

Adults (≥18 years of age) of both genders (except pregnant women),Should have been residing for at least one year in the selected village,No history of neuropsychiatric conditions that might hinder completion of neurobehavioral tests,No history of other conditions that are contraindications for performing Pulmonary function test (PFT) like presence of any active disease (e.g. pulmonary Tuberculosis, active haemoptysis, orofacial pain, acute respiratory infection including COVID-19 i.e. coronavirus disease caused by SARS-Cov-2 virus) or recent history (within previous 1 month) of myocardial infarction/aneurysm/surgery, etc.

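### Drawing villages without a size measure and then sampling in proportion to village population can lose precision that size-proportional draws with equal takes would keep

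*Protocol article*

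**What the plan says.** The text after Fig 3, under Sampling strategy, fixes three things.

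- Hemisphere totals: "2000 participants will be selected from the villages in the northern hemisphere while 1003 will be taken from the villages in the southern hemisphere".
- Stage 1: in each hemisphere, "a fixed number of villages will be selected randomly from those situated in each of the 0-2km, 2-5km and 5-10km zones". No size measure or selection probability is named, so equal chance is the plain reading, though it is not stated.
- Stage 2: "Total number of individuals sampled in each village will be proportionate to the total population of the selected village". Individuals are then invited at random from the village lists.

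Sample size calculation allows for the design with a single factor, "Deff = Design effect(1.25 for systematic sampling"). It has no separate term for clustering by village or for unequal takes. The article gives no village populations, no number of villages drawn or available per zone, and no intra-village correlation. The only village count is the 10 downstream villages for groundwater, which is not the participant sample.

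**The concern.** Two sampling schemes give residents of a zone about the same chance of selection. One draws villages with equal chance and samples in proportion to size, which is the plan. The other draws villages with probability proportional to size and takes the same number in each. They use the same number of villages and participants and differ in how evenly people are spread over villages.

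Under the plan a large village, once drawn, carries a large share of its zone's sample, so the chance character of that village weighs heavily in the zone's estimate. Under the alternative each drawn village carries equal weight. If people in the same village resemble each other in ECG findings, lung function or test scores, the plan's prevalence estimates and zone comparisons are less precise than they need be. The choice must be made before fieldwork, because it cannot be changed after recruitment.

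**Working it through.** **1. The plan's own figure.** Inputs from Sample size calculation: "p = Expected population proportion = 0.26; q = 1-p = 0.74"; z = 1.96; R = 0.30; Deff = 1.25; d = 0.02.

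- z²pq/d² = 1.96² × 0.26 × 0.74 / 0.02² = 1847.81
- 1847.81 × 1.30 × 1.25 = 3002.69, rounded up to 3003. The stated figure reproduces.

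**2. Room in the 1.25.** With equal takes of m per village, Deff = 1 + (m−1)·ICC, so Deff = 1.25 needs ICC = 0.25/(m−1). With m = 3003 divided by an assumed number of villages:

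- 10 villages: ICC about 0.0008
- 30 villages: about 0.0025
- 60 villages: about 0.005

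The factor leaves little room for clustering even with equal takes.

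**3. Effect of unequal takes.** With mean take m and takes proportional to size, Deff = 1 + ((1+CV²)·m − 1)·ICC. CV, ICC and m are all assumptions.

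At m = 150 and ICC = 0.02:

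- equal takes: 1 + 149 × 0.02 = 3.98; 3003/3.98 = 755
- CV 0.7: 1 + (1.49 × 150 − 1) × 0.02 = 5.45; 3003/5.45 = 551
- CV 1.0: 1 + (2 × 150 − 1) × 0.02 = 6.98; 3003/6.98 = 430

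Ratio of effective sample, proportional to equal takes, at the two ends of the assumed range:

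- m = 100, ICC 0.01: 1.99/2.24 = 89% (CV 0.5); 1.99/3.43 = 58% (CV 1.2)
- m = 150, ICC 0.05: 8.45/10.325 = 82% (CV 0.5); 8.45/19.25 = 44% (CV 1.2)

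As half-widths for p = 0.26, with 30 villages, ICC 0.01 and all 3003 responding: 2.21 points with equal takes, 2.35 at CV 0.5 and 2.71 at CV 1.0.

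**4. Dependence on the share of villages drawn.** The formula treats the drawn villages as a small sample from many. A simulation of one zone (667 people, 4 villages drawn, lognormal sizes, ICC 0.01) compared the plan with systematic size-proportional draws and equal takes everywhere. Design effects, plan against alternative:

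| Villages in zone | CV 0.5 | CV 1.0 |
|---|---|---|
| 30 | 2.67 / 2.35 | 3.13 / 2.19 |
| 10 | 2.20 / 1.84 | 2.50 / 1.69 |
| 5 | 1.42 / 1.35 | 1.52 / 1.38 |
| 4 (all taken) | 1.01 / 1.30 | 0.99 / 1.28 |

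The gap narrows as more of the zone is drawn. It reverses when every village is in, because the plan is then proportional stratified sampling.

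**5. With a rule for oversized villages.** A second simulation at ICC 0.02 took villages larger than the sampling interval with certainty and sampled them in proportion to size. Drawing 4 of 30 gave 3.5-4.1 for the plan against 2.8-3.0 for the alternative. Drawing 4 of 5 gave 1.6-1.8 against 1.1-1.3. With all villages taken the two tie.

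**The case against.** **Both designs are valid.** This stands. The plan's design is approximately self-weighting within a zone. It is only approximate because fixed hemisphere totals make the sampling fraction depend on which villages are drawn. A reader might infer that large villages bias the estimates; nothing in the article supports that.

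**Dominance by a few villages is not shown.** A reader might also infer that a few large villages will supply most of the 3003. The article gives neither village sizes nor counts. With lognormal sizes, the top three villages would supply on average 46% (CV 0.5) to 58% (CV 1.0) of the sample if there were 10 villages, but only 20% to 31% if there were 30.

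**The loss is conditional.** This also stands. From the stated radii, a half-disc of 0-2 km covers π × 2²/2, about 6 km². The 5-10 km half-ring covers π × (10² − 5²)/2, about 118 km². Taking all or nearly all villages is most plausible in the innermost zone, and there equal takes could do harm. That limits the remedy but does not remove the point, since with certainty villages handled properly the alternative ties at worst in the simulations.

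**Equal chance is inferred.** The article says only that villages are selected randomly, and a fuller protocol may specify the draw. If villages were in fact drawn in proportion to size, adding proportional takes would over-represent residents of large villages, so the method needs stating either way.

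**Clustering itself is the larger matter.** On the figures above, clustering with equal takes already moves 3003 to 755, and CV 0.7 moves it on to 551. Evening the takes would not restore a design effect of 1.25. Nor would it add exposure readings: air is monitored at identified or representative sites and groundwater in 10 downstream villages, so gains for exposure-effect estimates should not be overstated.

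**Conclusion.** The point holds as one of efficiency. Where only some of a zone's villages are drawn and their sizes vary, the stated combination inflates between-village variance by up to about 1+CV² compared with size-proportional draws and equal takes, for the same villages and participants.

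No single figure can be derived from the article. Under the assumed ranges (CV 0.5-1.2, ICC 0.01-0.05, 100-150 people per village) the effective sample is about 44-89% of that with equal takes. At the mild end the cost is small: 2.35 against 2.21 points of half-width. It disappears when every village in a zone is included. The absolute effective sizes also treat all 3003 as respondents, although 3003 already contains the 30% non-response inflation; on the plan's own formula, 3003/1.3 = 2310 would respond.

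The change is worth making because it is cheap and is only possible before the draw.

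**What to change.** Amend Sampling strategy as follows.

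- In each hemisphere and distance zone where villages are sampled, draw the fixed number with probability proportional to population (for example systematically) and invite an equal number in each drawn village.
- Join very small villages to a neighbour before the draw.
- Take any village larger than the sampling interval with certainty, and keep its take proportional to population.
- Keep proportional takes in zones where every village is included.
- Keep the totals of 2000 and 1003, and state how each is divided among the three zones.

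If the present scheme is kept, state that the village draw is equal-chance, give the number and sizes of villages per zone, and set the design effect for clusters of unequal size.

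Cost: population counts for all villages in a zone are needed before the draw, rather than for selected villages only. No participants or villages are added.
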